### Recruitment and enrollment

All consecutive patients presenting to the department of orthopedic surgery with LE who meet the inclusion criteria will be invited to participate in the trial. The treating surgeon or resident will introduce the trial to the patient and address the patient’s questions. Information will be handed to the patient to read at home. If the patient is willing to participate, informed consent will be obtained. Participants may take as long as they like to consider participation, provided that they still meet all eligibility criteria.

#### Randomization

After providing informed consent, eligible patients will be randomized by block randomization to one of the treatment arms, in order to have similar groups at any time.

Pain reduction seems dependent on the patient-reported activity or work-relatedness of this complaint [21, 22]. Therefore, patients with work related complaints have to be equally present in the intervention and in the care-as-usual groups. This is secured by block randomization using the following question:

#### My complaints of the elbow are caused or aggravated by my work (or household activities)

The answering categories are; totally agree, agree, agree nor disagree, disagree, totally disagree.

Patients are grouped in two groups;Totally agree, agreeagree nor disagree, totally disagree and disagree.

Two randomization lists will be conducted by computer by means of a pseudo random number generator, stratified into two strata to overcome differences in groups due to physical job demands.

The preparation of the randomization envelopes will be done by a research coordinator of the Amphia hospital, who is no member of the research team and the closed envelops will be distributed to the contributing hospitals. The envelopes will be opened in order of their consecutive numbers just before treatment.

#### Blinding

The treatment will be blinded for both the patient and outcome assessor (the specialized nurse, physiotherapist or trained resident). During the injection the patient will be blinded. Injectables will be blinded by a supporting nurse through the use of an opaque tape. The outcome assessors are different for each participating center. However, the outcome assessors are always blinded during all the follow up visits. The physician who performs the perforation does not have to be blinded, as long as he or she does not perform the follow-up visits.

#### Missing data

The primary outcome measure ‘pain’ will be plotted against the different follow up moments to determine whether the complete cases differ from the dropouts of the three groups. Potential differences are tested. Depending on whether there are significant differences associated with the drop-outs, a mixed model analysis with or without covariates will be used. For a mixed model analysis, no imputation of missings is required.

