### Statistical analysis

To compare groups the three groups (A – B, A – C and B - C) Chi-square tests will be used for categorical variables, and independent t-tests for continuous variables. The primary aim is to assess whether the reduction in pain for perforation with application of autologous blood or dextrose is more than 10 points compared to perforation only.

If so, a comparison will be made between the reduction in pain for perforation with application of autologous blood versus dextrose. A mean and a two-sided 98% confidence interval will be calculated. A mixed model will be used taking into account effects of time and treatment. The analyses are primarily performed according to the intention-to-treat principle.

In detail, data will be analyzed in the per protocol (pp) set as well as in the intention-to-treat (itt) set of patients. The pp-set consists of all patients, categorized according to the treatment eventually received, with non-missing observations on the pain VAS at all three visits during follow-up (8 weeks, 5 months and 1 year). The itt-set consists of all randomized patients.

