To get a better understanding, a linear mixed model analysis will be performed with the three repeated measurements of pain VAS as dependent variables. Along with treatment (a three-level nominal variable) the following covariables will be included in the model as independent variables: baseline pain VAS, the binary variable perceived aggravation of pain due to work ((totally) agree vs otherwise) and a three-level nominal variable time (visit number). Moreover, the interaction between treatment and time will be tested. If this interaction is not significant at the 0.01 level, then one overall treatment effect will be estimated assuming parallelism of the treatment effect. If this interaction turned out to be significant at the 0.01 level, then the effect of the 5 months’ visit will be considered the main effect of interest. Effects will be quantified by estimating two-sided 98% confidence intervals of the pair wise mean differences in pain VAS between the three treatment groups. Equivalence between two treatments is accepted if such a confidence interval is totally overlapped by the interval − 10 + 10. A restricted maximum likelihood estimation method will be used to estimate the coefficients so that missing values are properly imputed in order to meet the itt-condition. Under the pp-condition only patients with non-missing observations will enter the linear mixed model.

Similar analysis will be performed for functional recovery and quality of life. Otherwise the descriptives of the secondary outcome measures will be reported for the three groups.

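### Whether the mixed model adjusts for baseline pain and the work stratum is conditional on a dropout test in one section, fixed in another, and no analysis is named as primary

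*Protocol article*

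**What the plan says.** Four statements in the protocol article bear on how the treatment groups are compared.

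- **Missing data.** Pain is plotted over the follow-up visits "to determine whether the complete cases differ from the dropouts of the three groups. Potential differences are tested". The result decides the model: "Depending on whether there are significant differences associated with the drop-outs, a mixed model analysis with or without covariates will be used". The test, its level and the covariates are not given.
- **Statistical analysis, opening sentence.** For the pairwise comparisons of the three arms, "Chi-square tests will be used for categorical variables, and independent t-tests for continuous variables". The sentence is not restricted to baseline or descriptive data, and the primary aim follows directly.
- **Statistical analysis, next paragraph.** "A mixed model will be used taking into account effects of time and treatment". Neither baseline pain nor the stratum is mentioned.
- **Statistical analysis, later paragraph.** "the following covariables will be included in the model as independent variables: baseline pain VAS", together with "the binary variable perceived aggravation of pain due to work" and visit. This is the most fully specified model, and it carries the comparison of the 98% interval with ±10 points. Yet it is introduced as if supplementary: "To get a better understanding, a linear mixed model analysis will be performed".

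The Randomization section stratifies on work-relatedness and gives as its reason that pain reduction appears to depend on it. The Primary outcome section sets the main outcome as the change in provocation VAS at 5 months.

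**The concern.** A model without covariates cannot be the model that always contains baseline pain and the work stratum, so the Missing data rule and the later Statistical analysis paragraph cannot both be followed as worded. No sentence ranks the analyses.

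The conditional rule is also poorly founded. Baseline pain and the stratification factor are adjusted for because they predict the outcome and, for the stratum, because the randomisation used it. Neither reason weakens when dropouts happen not to differ from completers. The trigger also uses the primary outcome measure itself, so the form of the model would be settled after outcome data have been examined.

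Two things are at stake. One is the width of the interval that is compared with a 10-point margin. The other is the freedom to choose between adjusted and unadjusted results when nothing fixes which one counts.

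**Working it through.** **Inputs from the protocol.** Margin 10 mm, two-sided alpha 2%, 47 evaluable patients per arm, 55 randomised per arm (165 in total), 10% dropout. The normal quantile for a two-sided 2% level is 2.326 (the protocol prints 2.34).

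**Inputs not in the protocol.** The SD, the power and the correlation r between baseline and follow-up VAS. Everything below that uses them is illustrative.

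**The plan's own figure.** The 47 per arm cannot be reproduced without SD and power. Solving backwards for a 10 mm difference, SD = 10·√(47/2)/(2.326 + z_power). This gives 48.48/3.168 = 15.3 at 80% power and 48.48/3.608 = 13.4 at 90%.

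**Step 1: interval width.** Baseline adjustment multiplies the SD of a follow-up score by √(1−r²). An unadjusted change score has SD multiplied by √(2(1−r)). Unadjusted width relative to adjusted width is therefore 1/√(1−r²) for follow-up scores and √(2/(1+r)) for change scores.

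| r | Follow-up score, unadjusted | Change score, unadjusted |
|---|---|---|
| 0.3 | 1.05 | 1.24 |
| 0.5 | 1.15 | 1.15 |
| 0.6 | 1.25 | 1.12 |

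The stated endpoint is a change, so both columns matter. They run in opposite directions with r.

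**Step 2: half-width and equivalence power per pair.** Take n = 47 and r = 0.5, where the unadjusted follow-up and change scores have the same SD. With a true difference of zero, half-width = 2.326·SD·√(2/47) and power = 2Φ(10/(SD·√(2/47)) − 2.326) − 1, set to 0 if negative. The adjusted SD is SD·√0.75.

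| SD | Half-width, unadjusted → adjusted (mm) | Power, unadjusted → adjusted |
|---|---|---|
| 15 | 7.20 → 6.23 | 0.63 → 0.84 |
| 20 | 9.60 → 8.31 | 0.08 → 0.36 |
| 25 | 12.00 → 10.39 | 0 → 0 |

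Example at SD 15: 15·√(2/47) = 3.094, 10/3.094 = 3.232, 3.232 − 2.326 = 0.905, and 2·0.817 − 1 = 0.63. These are normal approximations for a single visit; the t distribution gives values lower by about 0.02 at SD 15. At SD 20, power to detect a 10 mm difference rises from 0.54 to 0.68.

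**Step 3: how the dropout rule would behave.** A simulation used 10,000 trials per scenario, 55 per arm, about 10% dropout, no treatment difference, and r of 0.3, 0.5 and 0.7. It compared baseline pain in dropouts and completers at an assumed 0.05 level, then tested two arms at 0.02 with or without baseline adjustment.

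- Dropout unrelated to baseline: the rule kept the covariate in about 5% of trials.
- Log-odds of dropout rising by 0.5 per SD of baseline pain: about 49%.
- Type I error when the rule is followed strictly: 0.018 to 0.022 against 0.02.
- Type I error when the smaller of the two p-values is picked freely: 0.025 to 0.038.

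**The case against.** The strongest reply is that the Missing data section never says which covariates it means. It ties them to differences associated with dropout, so it may intend extra covariates added to make the missing-at-random assumption more credible. The later paragraph's baseline pain and work stratum would then always stay. Likewise, the t-test sentence reads like a generic line for comparing groups, and the time-and-treatment sentence may be a summary of the model detailed later.

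All of this is possible, and it limits what can be said. A reader might infer that the plan will discard baseline pain and the stratum, or that it commits to three rival intervals for the primary contrast. The text establishes neither. But the rule contrasts a model with covariates and one without; it does not speak of additional covariates. The t-tests are not confined to description, and the detailed model is not called primary. The conflict between the Missing data rule and the later paragraph remains even if the t-test sentence is set aside.

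A reader might also infer that the dropout test has almost no power, so that the unadjusted branch is nearly certain. The simulation does not bear this out: under moderately informative dropout the test was significant in about half of trials. Which branch is likely depends on a dropout mechanism nobody knows yet.

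**Conclusion.** The point holds as an unresolved conflict over the primary analysis. One section makes covariates conditional on a dropout test, another fixes them, a third statement omits them, and none is ranked. Read literally, the conditional rule can drop a prognostic baseline value and the randomisation stratum for a reason unrelated to their value.

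The conflict is textual and rests on no assumption. Its size does rest on assumptions. The loss of precision is 5% to 25% of interval width over r = 0.3 to 0.6, with the direction of the trend depending on whether follow-up or change scores are analysed. The effect on equivalence power is substantial at SD 15 or 20 and nil at SD 25, where neither interval fits inside the margin. No single power gain should be quoted as the consequence for this trial.

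It would be tempting to conclude that the data-driven rule inflates type I error. Followed strictly, it hardly does. Inflation appears only if the more favourable of the adjusted and unadjusted results is chosen, which the present wording does not rule out.

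**What to change.** 1. In Missing data, delete the rule that decides between a model with and without covariates.
2. In Statistical analysis, name the detailed linear mixed model as the primary analysis. State that it always includes baseline provocation VAS and the work-aggravation stratum, whatever the dropout pattern. Make the shorter mixed-model sentence refer to it.
3. Label the t-tests and chi-square tests as descriptive.
4. Keep the comparison of dropouts with completers, but use it only to inform missing-data sensitivity analyses, for example adding dropout-related covariates to the primary model.

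The rule for the treatment-by-time interaction is a separate matter and is left as it stands. The cost is wording only: baseline VAS and the stratum are already collected, and neither sample size nor visits change.

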### Statistical analysis

To compare groups the three groups (A – B, A – C and B - C) Chi-square tests will be used for categorical variables, and independent t-tests for continuous variables. The primary aim is to assess whether the reduction in pain for perforation with application of autologous blood or dextrose is more than 10 points compared to perforation only.

If so, a comparison will be made between the reduction in pain for perforation with application of autologous blood versus dextrose. A mean and a two-sided 98% confidence interval will be calculated. A mixed model will be used taking into account effects of time and treatment. The analyses are primarily performed according to the intention-to-treat principle.

In detail, data will be analyzed in the per protocol (pp) set as well as in the intention-to-treat (itt) set of patients. The pp-set consists of all patients, categorized according to the treatment eventually received, with non-missing observations on the pain VAS at all three visits during follow-up (8 weeks, 5 months and 1 year). The itt-set consists of all randomized patients.

To get a better understanding, a linear mixed model analysis will be performed with the three repeated measurements of pain VAS as dependent variables. Along with treatment (a three-level nominal variable) the following covariables will be included in the model as independent variables: baseline pain VAS, the binary variable perceived aggravation of pain due to work ((totally) agree vs otherwise) and a three-level nominal variable time (visit number). Moreover, the interaction between treatment and time will be tested. If this interaction is not significant at the 0.01 level, then one overall treatment effect will be estimated assuming parallelism of the treatment effect. If this interaction turned out to be significant at the 0.01 level, then the effect of the 5 months’ visit will be considered the main effect of interest. Effects will be quantified by estimating two-sided 98% confidence intervals of the pair wise mean differences in pain VAS between the three treatment groups. Equivalence between two treatments is accepted if such a confidence interval is totally overlapped by the interval − 10 + 10. A restricted maximum likelihood estimation method will be used to estimate the coefficients so that missing values are properly imputed in order to meet the itt-condition. Under the pp-condition only patients with non-missing observations will enter the linear mixed model.

Similar analysis will be performed for functional recovery and quality of life. Otherwise the descriptives of the secondary outcome measures will be reported for the three groups.

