### Sample size and power calculation

A reduction in pain of at least 10 mm on a 0–100 mm visual analogue scale is deemed a clinical significant improvement. Due to the three study arms of our RCT, there are also three null hypotheses tested:| A - B | ≥ 10 | A - C | ≥ 10 and | B - C | ≥ 10 points on the VAS pain scale, according to a superiority design. In which A, B and C stands for dextrose, autologous blood and perforation only respectively. A number of 47 patients is required in each trial arm when a two-sided 98% confidence interval is used, with a two-sided alpha of 2%, corresponding to a z-value of 2.34 (J Scott Armstrong: Tables for Statistical Significance with Multiple Comparions). To adjust for a maximum of 10% dropout over the one year follow up period, 55 patients will be included in each of the three trial arms. Therefore, a total of 165 patients are needed. It is expected that each week in both hospitals a total of 3 patients can be included. Therefore, the inclusion period takes about 55 weeks. Patients that are withdrawn from the study will not be replaced, since there is accounted for these dropouts in the power analysis.

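### The primary aim asks for a benefit of more than 10 points, the same 10 mm that defines clinical significance, and no rule says how superiority is concluded

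*Protocol article*

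**What the plan says.** All references are to the protocol article.

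- **Sample size and power calculation.** A reduction of at least 10 mm on the 0–100 VAS "is deemed a clinical significant improvement". The section then lists three null hypotheses, each that the absolute difference between two arms is at least 10 "points on the VAS pain scale, according to a superiority design". The error rate is set "with a two-sided alpha of 2%, corresponding to a z-value of 2.34". "A number of 47 patients is required in each trial arm when a two-sided 98% confidence interval is used". No SD, power or expected true difference is given.
- **Statistical analysis, opening paragraphs.** Independent t-tests are named for continuous variables in the three pairwise comparisons. The primary aim is whether the reduction with "autologous blood or dextrose is more than 10 points compared to perforation only". The blood-versus-dextrose comparison follows only if that is so. "A mean and a two-sided 98% confidence interval will be calculated".
- **Statistical analysis, mixed-model paragraph.** Two-sided 98% intervals are estimated for all pairwise differences. Equivalence is accepted when such an interval lies wholly within −10 to +10. No matching rule is given for superiority.
- **Background and Study design.** The declared hypothesis is that perforation only and perforation with an injectable do not differ in effectiveness. The design is called superiority.

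**The concern.** Ten millimetres has two incompatible jobs. In the sample size section it is the difference worth detecting. In the primary aim it is the value that the difference must exceed. A trial planned to detect 10 mm tests against zero and expects to succeed when the truth is 10 mm. A trial that must show more than 10 mm needs a true effect well beyond 10 mm to have useful power.

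The nulls add a second conflict. Rejecting a null of an absolute difference of at least 10 leads to the conclusion that the arms differ by less than 10. That is equivalence, not superiority.

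At stake is how the primary result is declared. The same data could be called a success or a failure depending on which reading the analyst adopts, and the choice also decides whether blood and dextrose are compared at all.

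**Working it through.** **Inputs from the protocol article.** Threshold 10 points (Statistical analysis). Clinically significant difference 10 mm, two-sided alpha 2%, 47 per arm before dropout (Sample size and power calculation). Two-sided 98% interval (both sections).

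**Assumed input.** The SD, because none is stated. For the same reason, and because power is missing, the figure of 47 cannot be reproduced directly. It can only be solved backwards. If 47 per arm was meant to give 80% power at 10 mm against zero:

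SD = 10 × √(47/2) / (2.326 + 0.842) ≈ 15.3 mm.

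At 90% power the implied SD is 13.4 mm. Normal approximation throughout, with SE = SD × √(2/47). This gives SE = 3.16 at SD 15.3, 4.13 at SD 20 and 5.16 at SD 25.

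**Reading 1: the 98% interval must lie above 10.**

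P(lower limit > 10 | true d) = 1 − Φ(2.326 − (d − 10)/SE)

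At d = 10 the last term vanishes, so the probability is 1 − Φ(2.326) = 1.0%. Neither SD nor n enters. With the stated z of 2.34 it is 0.96%.

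| | SD 15.3 | SD 20 | SD 25 |
|---|---|---|---|
| Success at true 10 mm | 1% | 1% | 1% |
| Success at true 15 mm | 23% | 13% | 9% |
| Success at true 20 mm | 80% | 54% | 35% |
| True difference for 80% power, 10 + (2.326 + 0.842) × SE | 20.0 mm | 23.1 mm | 26.3 mm |
| For contrast: power against zero at true 10 mm | 80% | 54% | 35% |

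If both injectables truly give 10 mm, the chance that at least one passes is 1.9% (correlation 0.5 through the shared perforation-only arm). That is how often the blood-versus-dextrose step would be reached.

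**Equivalence at the same truth.** The rule needs the estimate plus 2.326 × SE to be below 10. At d = 10 this has probability Φ(−2.326) = 1.0%, and the lower bound of −10 can only reduce it. So at a true 10 mm benefit superiority is concluded 1% of the time, equivalence at most 1%, and neither about 98% of the time.

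**Reading 2: the point estimate is compared with 10.**

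P(estimate > 10 | true d) = 1 − Φ((10 − d)/SE)

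- d = 10: 50% at any SD. For at least one of two injectables, 67%.
- d = 5: 5.7% / 11.3% / 16.6% at SD 15.3 / 20 / 25.
- d = 0: 0.08% / 0.8% / 2.6% at the same SDs.

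None of these rates is set by the 2% alpha.

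**Reading 3: a test against zero, with 10 mm as the planning difference.** Under this reading the problem disappears (last row of the table). The aim sentence does not say this, and neither do the nulls.

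**The case against.** The strongest reply is that the protocol nowhere requires the lower limit, or the estimate, to exceed 10. The sentence states an aim, not a rejection rule. The t-tests named just before it would ordinarily be against zero, so reading 3 may well be what was meant. This stands in part: the 1% figure describes one literal reading, not a rule that the protocol adopts. But the aim puts the threshold at 10 and makes a further comparison depend on it, and the nulls are also written at 10. Nothing in the text selects reading 3.

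It is also fair to say that any margin test with a 98% interval succeeds 1% of the time exactly at its margin, and that a margin can be a deliberate strict choice. That would be an answer if the margin were smaller than the effect the plan calls clinically significant. Here the two are the same number.

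Four stronger inferences are tempting, and the documents do not support them:

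- *47 per arm is too small for the margin at any plausible SD.* No SD, power or expected true difference is stated, so this cannot be shown. At SD 15.3 power against the margin is 80% if the truth is 20 mm.
- *Missing the threshold favours the no-difference hypothesis by construction.* The equivalence rule needs the whole interval inside ±10, and failing to exceed 10 does not meet it. The usual result would be inconclusive.
- *An injectable worse than perforation only would go unnoticed.* Only the aim sentence is one-directional. The intervals are two-sided for all pairs, so harm would be visible, though no rule turns it into a conclusion.
- *The point-estimate reading yields many false claims.* At a true zero difference they stay between about 0.1% and 3% for SDs of 15.3 to 25. The rate is not governed by alpha, but it is not necessarily large.

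**Conclusion.** The point holds as a contradictory decision threshold. It is not a matter of detail left to an analysis plan, because the threshold is stated, and it conflicts with the role of 10 mm in the sample size section and with the superiority label on the nulls.

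At a true 10 mm benefit the two literal readings succeed 1% (interval) and 50% (point estimate) of the time. Both figures are free of any assumption about SD or sample size. The statement that 80% power on the interval reading needs a true benefit of about 20 mm assumes that 47 per arm was sized for 80% power at 10 mm against zero, with an implied SD of about 15.3. With larger assumed SDs the required benefit is larger.

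The documents do not show that the primary aim is unattainable or that the trial is biased towards no difference. They show that the conclusion drawn from a clinically significant benefit is undetermined and, on the interval reading, almost always inconclusive.

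**What to change.** 1. **Statistical analysis, primary aim.** State that an injectable is superior (or inferior) to perforation only if the two-sided 98% interval for the difference in provocation VAS at 5 months excludes 0. Make the blood-versus-dextrose step depend on that rule.
2. **Sample size and power calculation.** Restate the superiority nulls as zero difference, with 10 mm as the difference to be detected.
3. **Role of 10 mm.** Keep it as the clinical-relevance yardstick when the estimate and interval are described, and as the margin of the existing equivalence rule.

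The mixed-model paragraph should be read against item 1, since it reports one overall treatment effect unless the interaction with time is significant, while the primary endpoint is at 5 months.

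The cost is a few sentences in two sections, with no change to data collection or sample size. The downside is that a statistically superior result may be smaller than 10 mm. Reporting the interval against 10 mm makes that plain.

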#### Primary outcome

The main outcome measures are the changes in pain using a Visual Analog Scale (VAS, 0–100) [9]. The VAS consists of a 100-mm horizontal numbered line anchored at one end (0) with the words “no pain” and at the other end (100) with the words “worst pain imaginable.” Patients are asked to score their pain on this line during rest (at time of measure), provocation and maximum grip strength. The provocation test is conducted on the outpatient clinic by resisted dorsiflexion of the wrist during full elbow extension. The VAS pain scores will be measured at baseline and 8 weeks, 5 months and 1 year after treatment.

The main outcome measure is the change in VAS when performing the provocation test 5 months after treatment.

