#### Crossover

Patients treated with perforation without infiltration which could not be classified as “success” should also be treated with infiltration with autologous blood, a so called one arm crossover. This is currently the most common treatment of LE in OLVG and Amphia hospital. A treatment is classified as a success when there is a reduction of pain of 10 points (0-100 mm VAS score) 5 months after the treatment compared with baseline. If the treatment wasn’t successful after 5 months the given treatment can be looked up in an encrypted list; this list only shows if the patient has had an infiltration or perforation, without the specification of the injectable. After the crossover moment, patient data will be collected as described above.

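### The per-protocol set groups patients by the treatment eventually received, so perforation-only failures who cross over count as blood and the per-protocol contrasts are biased towards perforation only

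*Protocol article*

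**What the plan says.** Four statements in the protocol article bear on this.

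- **Primary outcome.** "The main outcome measure is the change in VAS when performing the provocation test 5 months after treatment".
- **Crossover.** Perforation-only patients who are not a success "should also be treated with infiltration with autologous blood, a so called one arm crossover". The criterion is: "A treatment is classified as a success when there is a reduction of pain of 10 points", judged at 5 months against baseline. No other arm crosses over. Follow-up continues: "After the crossover moment, patient data will be collected as described above".
- **Statistical analysis, sets.** "The analyses are primarily performed according to the intention-to-treat principle", and the data are also analysed per protocol. The per-protocol rule is: "The pp-set consists of all patients, categorized according to the treatment eventually received, with non-missing observations on the pain VAS at all three visits", where the visits are 8 weeks, 5 months and 1 year.
- **Statistical analysis, model.** Both sets enter the same linear mixed model of the three follow-up scores, with treatment as a single three-level variable. Pairwise differences get 98% confidence intervals, and two treatments are accepted as equivalent if the interval lies within -10 to +10 mm.

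**The concern.** The set needs a score at 1 year, so it closes 7 months after the crossover decision. By then a perforation-only failure who crossed over has, in the ordinary sense of the phrase, eventually received blood. The model has one fixed treatment label per patient, and nothing splits or stops a patient's data at crossover. Such a patient's 8-week and 5-month scores would therefore be analysed as blood scores, although no blood had been given when they were recorded.

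Perforation only then keeps its 5-month successes plus any failures who did not cross over, and blood takes in the other arm's failures. Group membership depends on the outcome, so the direction of the bias is fixed. Adjustment for baseline VAS, work aggravation and visit does not remove it. The contrasts with dextrose are distorted too, because both other groups have changed composition.

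This matters because the stated hypothesis is no difference and the plan contains an equivalence rule. A reader would use the per-protocol result to check an intention-to-treat equivalence finding. Here it could contradict a sound finding, or hide a benefit of blood, through misclassification alone.

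**Working it through.** **Inputs from the article.** Crossover threshold 10 points at 5 months; margin 10 mm; 98% interval; 47 patients per arm before dropout.

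**Inputs not in the article, hence assumed.** Mean 5-month reduction 20 to 40 mm and SD 15 to 30 mm, normally distributed and identical in all arms (no true difference). To begin with, every failure crosses over and the crossover rule uses the provocation VAS. The article gives no figure of its own for this bias, so there is none to reproduce. Its 47 per arm cannot be reproduced either, as neither SD nor power is stated; with a 10 mm difference and two-sided alpha of 2% it would fit an SD of about 15 if power were 80%.

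**Formulas.** Let the reduction have mean m and SD s, and let a = (10 - m)/s.

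- Proportion failing: p = Φ(a)
- Mean of those kept in perforation only: K = m + s·φ(a)/(1 - p)
- Mean of those moved: M = m - s·φ(a)/p
- Mean of the enlarged blood group: B = (m + p·M)/(1 + p)
- Spurious difference: K - B

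**Worked case, m = 25, s = 25.** a = -0.6, φ(a) = 0.333, p = 0.274. K = 25 + 25 × 0.333/0.726 = 36.5. M = 25 - 25 × 0.333/0.274 = -5.4. B = (25 - 0.274 × 5.4)/1.274 = 18.5. Difference = 36.5 - 18.5 = 18.0 mm, with a true difference of zero.

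**Spurious 5-month difference in favour of perforation only (mm), full uptake:**

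| Mean reduction | SD 15 | SD 20 | SD 25 | SD 30 |
|---|---|---|---|---|
| 20 | 10.2 | 15.6 | 20.9 | 26.2 |
| 25 | 7.4 | 12.7 | 18.0 | 23.3 |
| 30 | 5.0 | 9.9 | 15.2 | 20.5 |
| 35 | 3.0 | 7.4 | 12.4 | 17.6 |
| 40 | 1.6 | 5.2 | 9.8 | 14.9 |

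The bias exceeds 10 mm in 12 of the 20 cells. It is small where few patients fail: at 40/15 only 2% cross over.

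**Dextrose contrasts.** At 20/15, K = 26.4 and B = 16.2 against an undisturbed dextrose mean of 20. Perforation only gains 6.4 mm on dextrose, and blood loses 3.8 mm.

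**Partial uptake.** With uptake u, replace p by q = u·p in B, and the kept mean becomes (m - q·M)/(1 - q). At u = 0.5 the bias is 4.9 mm at 20/15 and 8.5 mm at 25/25, about half.

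**Consequences for the interval.** A simulation (2,000 trials, 47 completers per arm, correlation 0.5 between visits, 8-week mean 70% of the 5-month mean) gave these results for the 5-month 98% interval with no true difference:

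| Mean/SD | Excludes zero | Equivalence accepted | Equivalence accepted, grouped by first treatment |
|---|---|---|---|
| 20/15 | 87% | 0.2% | 60% |
| 30/15 | 22% | 23% | 60% |
| 40/15 | 4% | 55% | 61% |

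The nominal rate for excluding zero is 2%. At SD 25 equivalence is almost never accepted under either grouping, but zero is still wrongly excluded in 98% (mean 20) and 76% (mean 30) of trials.

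**Average over three visits.** If the treatment-by-time interaction is not significant, the plan estimates one overall effect. The bias is then about two thirds as large: 6.7 mm at 20/15 and 13.9 mm at 20/25. If the second treatment brought a 20 mm benefit at 1 year, these become 5.5 and 12.2 mm.

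**The case against.** **Intention-to-treat is primary.** This is correct and limits the point. Relabelling crossovers cannot move a comparison by randomised arm. A reader might infer that the trial's main result is biased; the article does not support that.

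**The phrase may mean the treatment given at the first session, as opposed to the one allocated.** This is possible. The text does not say so, however, and in a protocol with a planned later treatment, plus a set that closes at 1 year, the word points to the final treatment. If the first session was meant, the wording still needs correcting.

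**Data collection after crossover may mean a new 8-week, 5-month and 1-year series.** The blood group would then hold scores taken after blood, and the calculation for that group would not apply. Perforation only would still lose its failures: its mean would rise from 20 to 26.4 at 20/15, and from 25 to 36.5 at 25/25.

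**The success rule does not say which VAS it uses.** The article collects pain at rest, at provocation and at maximum grip. It is therefore not established that the primary outcome itself triggers crossover. If another VAS does, and has the same mean and SD, the bias scales with the correlation of the two changes: at an assumed 0.5, 18.0 mm becomes 9.0 mm.

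**Direction.** The bias favours perforation only, so it cannot produce a false finding that blood is better than perforation only by more than 10 points. It can hide such a benefit or block a per-protocol equivalence conclusion. That stands as a limit on the harm.

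**Conclusion.** The rule as written lets the 5-month outcome decide the per-protocol group. It biases the blood contrast in favour of perforation only and distorts both dextrose contrasts. The direction follows from the text. The size does not, because the SD, expected change and crossover uptake are not given.

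With no true difference, full uptake and the provocation VAS as trigger, the 5-month bias lies between 1.6 and 26 mm. It is about half that at 50% uptake, about two thirds when averaged over the visits, and smaller if a different VAS is the trigger. A reader might infer that the per-protocol analysis is bound to show a spurious difference larger than the 10 mm margin. That happens over much of the assumed range, but not where few patients fail or few cross over, so it cannot be stated without condition.

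This should be fixed. It is a fault in a secondary analysis set that shares the primary model and the equivalence rule, and the primary intention-to-treat analysis does not depend on it.

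**What to change.** Rewrite the per-protocol definition in the Statistical analysis section so that:

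- the set consists of patients who received their randomised treatment at the first procedure, analysed in that arm;
- crossover never reclassifies a patient;
- observations after crossover are not used in this set;
- only the baseline and 5-month provocation VAS are required, instead of scores at all three follow-up visits, since the main time point is 5 months.

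In the simulation, grouping by first treatment brought the mean 5-month difference back to 0.0 to 0.2 mm under no true effect, and the 98% interval excluded zero in about 2% of trials. The cost is one paragraph of wording. Treatment, visits and data collection do not change.
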